### Identification of eligible patients

Participants will be recruited from acute sites and community rehabilitation teams in NHS Lanarkshire, UK. For full inclusion/exclusion criteria refer to Table 1. Potential participants will be identified by their NHS direct care team and/or stroke research nurses, who will ensure that the patient is able to give informed consent with suitable communication support if required. Written informed consent will be obtained from all participants prior to participation in the study.

**Table 1 T1:** Inclusion and exclusion criteria

**Inclusion criteria**	**Exclusion criteria**
· Clinical diagnosis of stroke	· Severe visual or cognitive problems precluding participation in the study
· In the subacute stage of stroke (≤3 months since stroke onset)	· Involved in another physical rehabilitation research trial
· Of either gender	· Pre-existing lower limb deficits or any other medical comorbidities that interfere significantly with gait.
· Age ≥18 years	
· Exhibit an abnormal gait pattern Functional Ambulation Category of 1 or more	
· Medically stable and hence suitable for physical rehabilitation	
· Able to understand and follow simple instructions	
· Able to give informed consent when assisted to do so with suitable communication aids if required	

The research nurse or researcher will go over the study’s participant information sheet with the patient. Patients will have the opportunity to ask any questions and will be given a minimum of 24 hours to review the information sheet and consider their participation in the trial. During this time they will be able to ask any further questions and talk to other people about the study. The research nurse or researcher will then approach the patient again, answer any further questions and, if appropriate, gain consent from the patient who is to sign a consent form. This study complies with data-protection legislation. Upon enrolment in the study, patients will be allocated a unique trial number that will be used in all case-report file documents. Patient names will be used to arrange appointments only and will not be used for data-collection purposes. Where a patient is deemed eligible and provides informed consent, the following demographic and stroke information will be collected: age, sex, postcode, date of stroke, side affected, dominant side, pre-stroke function (FAC score) and type of stroke (Oxford Stroke Classification) [18].

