### Randomisation method

The randomisation sequence will be generated using an independently verified S-PLUS program (Robertson Centre for Biostatistics, University of Glasgow, UK). This program uses a stratified permuted block randomisation procedure, with stratification based on the severity of walking impairment. This stratification will ensure that intervention groups are balanced, since severity of impairment influences the potential for recovery. Severity of walking impairments will be classified using the FAC. Stratification will consist of two groups: FAC 1 to 3, and FAC 4 to 5. The researcher will access intervention allocations through the study web portal, designed and maintained by The Robertson Centre for Biostatistics at the University of Glasgow. The randomisation sequence will be concealed until the participant’s details are logged on the system.

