### Statistical analysis

Data will be analysed on an intention to treat basis. Data will be held independently on a database at the Glasgow Clinical Trials Unit at the University of Glasgow. Datasets for each randomisation allocation will be compared by independent blinded assessors.

Descriptive statistics will be calculated and the characteristics of the population will be described. Two mixed-design analysis of variance models will be used to test for mean differences between the three arms of the RCT, while subjecting participants to repeated measures. The repeated measures will be examined for differences over time and between groups. If appropriate, factors that may affect the outcome of the trial – such as differences in time since onset of stroke, age, severity of stroke or memory and attention levels – will be investigated using demographic and stroke-related information collected at baseline.

Data collected from pre-trial and post-trial interviews by the study researcher and in-depth semi-structured interviews by an independent researcher will be suitably coded such that qualitative responses can be categorised and explored.

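### Time since stroke, which the plan itself lists as a possible influence on outcome, should be a fixed term in the walking-speed analysis instead of an optional one

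*Protocol article*

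**What the plan says.** Four statements in the protocol article bear on this.

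- **Entry** (Identification of eligible patients, Table 1): "In the subacute stage of stroke (≤3 months since stroke onset". No lower limit in days is given, although participants must also be "Medically stable and hence suitable for physical rehabilitation" and have a FAC of at least 1. Date of stroke is recorded at baseline.
- **Randomisation** (Randomisation method): permuted blocks, "with stratification based on the severity of walking impairment". "Stratification will consist of two groups: FAC 1 to 3, and FAC 4 to 5". The reason is prognostic: "since severity of impairment influences the potential for recovery".
- **Main analysis** (Statistical analysis): "Two mixed-design analysis of variance models will be used to test for mean differences between the three arms of the RCT". No covariate is named.
- **Other influences** (same section): "If appropriate, factors that may affect the outcome of the trial" are to be investigated, with the examples "such as differences in time since onset of stroke, age, severity of stroke or memory and attention levels". The text does not say what would make this appropriate, or whether investigating means adjusting the main result.

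**The concern.** Patients at this stage are still recovering, and how fast they recover plausibly depends on how long ago the stroke was. Under the entry rule, one participant's 6-week treatment period may begin early in recovery and another's near the 3-month limit. The FAC bands do not separate the two: an early and a late entrant with the same FAC fall in the same stratum. The protocol stratifies on FAC because it predicts recovery, and it names recovery stage as a likely influence too, yet it fixes no place for the latter in either the design or the model.

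Three things are at stake: precision, protection of the one realised trial against a chance difference in recovery stage, and freedom from a choice of model made after the data are seen. They matter because the article intends the results to size a definitive trial, so a distorted effect estimate or a needlessly large residual variance would carry forward.

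**Working it through.** The plan gives no figure for time since onset, so there is none to reproduce. The only design input is 15 participants per arm (Sample size). All else below is a labelled assumption.

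**1. Chance imbalance, without assuming a spread.** In SD units of time since stroke, the difference between two arm means has standard error √(2/15) = 0.365.
- A given pair differs by more than 0.5 SD: 0.5/0.365 = 1.37, two-sided probability 17%.
- At least one of the three pairs differs by more than 0.5 SD: 36% (simulated). By more than 0.7 SD: 13%.

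**2. The same in weeks, under two assumed spreads.**
- Entry uniform over 0 to 13 weeks: SD = 13/√12 = 3.75 weeks; SE = 3.75 × 0.365 = 1.37 weeks; 95% range about ±2.7 weeks. Chance of a gap over 2 weeks for a given pair: 2/1.37 = 1.46, about 14%.
- SD of 15 days: SE = 15 × 0.365 = 5.5 days. Chance of a gap over 14 days: 14/5.5 = 2.55, about 1%.

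The gap in weeks therefore depends heavily on an entry distribution that the document does not give.

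**3. Error rates.** 40,000 null trials were simulated with three arms of 15. Change was analysed by one-way ANOVA, and again with time since stroke as a covariate. The correlation r between time since stroke and change is assumed.

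| r | Unadjusted, all trials | Unadjusted, given some pair differs by >0.7 SD | Smaller of the two p-values | Covariate fixed in advance |
|---|---|---|---|---|
| 0 | 5.1% | 5.2% | 5.8% | 5.1% |
| 0.3 | 5.0% | 7.2% | 6.6% | 5.1% |
| 0.5 | 5.0% | 11.5% | 7.5% | 5.1% |
| 0.7 | 5.0% | 18.8% | 8.4% | 5.1% |

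In the trials with the large imbalance, the fixed covariate gives 5.0%. The smaller-p column is a worst case for choosing the model afterwards.

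**4. Shift in the estimate.** An imbalance of 0.5 SD moves the unadjusted difference by 0.5 × r SD of the change: 0.15, 0.25 and 0.35 SD at r = 0.3, 0.5 and 0.7.

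**5. Precision.** If time since stroke explains a share R² of residual variance, the gain in effective sample size is 1/(1 − R²) − 1.
- R² = 5%: 1/0.95 − 1 = 5%.
- R² = 10%: 1/0.90 − 1 = 11%.
- R² = 20%: 1/0.80 − 1 = 25%.

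**6. Where the term must enter.** In a repeated-measures model, a baseline covariate entered only as a main effect shifts all of a participant's visits equally. With complete data it then drops out of the group-by-time comparison, which is where unequal recovery would show. A covariate-by-time term is needed.

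**The case against.** A reader might infer that spontaneous recovery can pass as a treatment effect. The document does not support that. The three arms are randomised concurrently and one receives usual care, so recovery common to all arms cancels. The unadjusted test already allows for chance imbalance, and its error rate stays at 5% in the second column of the table. The figures of 7% to 19% apply only to the 13% or so of trials with a large imbalance.

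It is also tempting to read the Statistical analysis section as saying that the main result will be adjusted if an imbalance is noticed. It does not say so: an unadjusted main analysis followed by exploratory work fits the words as well. The smaller-p figures show what the open wording would permit, not what is planned.

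Nor does entry run literally from onset. Medical stability, the FAC requirement and at least 24 hours to consider consent exclude that, so the 0-to-13-week spread is at the wide end.

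Finally, choosing covariates is ordinary SAP work, the SAP is not shown, and the trial is exploratory. This limits the weight of the point but does not remove it, because the article is not silent. It states a conditional rule covering five factors (time, age, severity, memory, attention). Those factors alone allow 2⁵ = 32 covariate sets, with no criterion for choosing among them.

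**Conclusion.** The point stands as a cheap improvement. The trial is not systematically biased by leaving time since stroke out of the design and the fixed model. What it loses is precision, protection against a chance difference in recovery stage, and a closed choice of model.

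The firmest figure is the 17% chance of a gap above 0.5 SD between a given pair of arms, which needs only the 15 per arm and normal theory. The precision gain of about 5% to 25% rests on an assumed 5% to 20% of residual variance explained, and the probabilities in weeks rest on an assumed entry distribution. The document gives neither, and nothing in it allows the imbalance to be converted into walking speed.

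**What to change.** In the Statistical analysis section, take time since stroke out of the conditional sentence and state that:

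- time from stroke to baseline assessment will be included in the primary walking-speed analysis regardless of observed balance;
- it will enter the repeated-measures model with its interaction with time or, alternatively, as a covariate in an ANCOVA of follow-up speed on arm and baseline speed;
- its scale, linear or log, is fixed in advance. The document gives no basis for preferring either.

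Age, memory and attention can stay exploratory. A second stratifier is not needed and would make the strata sparse with 45 participants.

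The cost is a short change of text and one or two degrees of freedom, depending on how many visits the model covers. Date of stroke is already collected, so no new data are needed, and recruitment and treatment do not change.

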## Discussion

This protocol describes a phase II (or exploratory) RCT that aims to explore the effect of using visual feedback of biomechanical movement performance as an adjunct to gait training after stroke. Stroke survivors and stroke rehabilitation professionals, clinicians and academics, have been involved in both the development of this protocol and the visualisation software. Our findings from informal semi-structured interviews and focus groups have suggested that dynamic visualisations could be a useful addition to gait rehabilitation after a stroke. Involving users in the development of the software has meant visualisations have been designed to specifically complement lower-limb stroke rehabilitation.

Therapy and outcome sessions could possibly be influenced by the knowledge and experience of individual therapists. To reduce this variability, one physiotherapist will lead all trial therapy sessions that are provided in addition to the patient’s usual care.

The trial will focus on quantitative functional outcomes; however, it will incorporate qualitative measures, including patient-reported questionnaires, to aid in the explanation of outcomes. Qualitative data capture will be analysed to provide clarity on the impact of the visualisations with regards to participant confidence, motivation and understanding of their rehabilitation programme as a result of taking part in the trial. This single-site study, although relatively small scale, is expected to provide valuable evidence to support the early mobilisation of stroke survivors through visualisation of movement performance. We anticipate that results will confirm benefits associated with using visualisation of biomechanical data during gait training after stroke, and will be used to power a future larger-scaled study.

Furthermore, the RCT aims to address whether the visualisations will engage clients in their rehabilitation, enabling them to perform to their optimal functional capability. This method retains the accuracy and accessibility of the biomechanical data required by clinicians but presents the data in a nontechnical way, facilitating enhanced communication between patient and physiotherapist and patient understanding of their rehabilitation. Patients will be able to see how they move and will be able to observe any compensatory strategies they may employ to complete rehabilitation tasks. This application has the potential to enable patients to self-correct their movement patterns and discourage overreliance on their physiotherapists for corrective advice. Moreover, such a stroke rehabilitation tool could provide the objective training required for assessment during rehabilitation. Tracking progress after a stroke can be difficult as improvements can be small and can take place over long periods of time. Retaining movement data over the rehabilitation programme enables one to compare different therapy sessions. For example, a physiotherapist could visually view progress between baseline and consequent sessions by pulling up saved files that display stick figure visualisations mimicking how the user moved in those particular sessions. This visualisation could instantly allow the physiotherapist to get an idea of the quality of the patient’s movements, and supporting numerical data could also be accessed to compare ranges of motion achieved over time.

### Trial status

Ethical approval was obtained from NHS West of Scotland Research Ethics Committee 2 on 26 April 2011 (Ref 11/AL/0184). NHS Lanarkshire R&D approval was obtained on 5 April 2011. The trial commenced in March 2012.

## Abbreviations

3D : three-dimensional; FAC : Functional Ambulation Category; NHS : National Health Service.
